### Randomisation and interventions

A total of 184 participants will be randomly allocated to receive either canagliflozin or metformin treatment (1:1). The randomization operation will be generated by an independent statistician, who will ensure the balance of participants according to age, sex, HbA1c and BMI and course of their disease when grouping, and a code list will be directly allocated to the main investigators of every center. The intervention content of the two groups is as follows.

Canagliflozin treatment group: For oral treatment, the participants will receive canagliflozin tablets (Janssen-Cilag S.p.A., Ltd., National Drug Approval: H20170375) once daily, 100–300 mg per time, with a minimum dose of 100 mg per day and maximum dose of 300 mg per day.Metformin treatment group: For oral treatment, the participants will receive metformin hydrochloride tablets (Sino-American Shanghai Squibb Pharmaceutical Co., Ltd., National Drug Approval: H20023370 (0.5 g × 20 tablets)/Sino-American Shanghai Squibb Pharmaceutical Co., Ltd., National Drug Approval: H20023371 (0.85 g × 10 tablets × 2 plates)), 1–3 times a day, 500–2000 mg per time, with a minimum dose of 500 mg per day and maximum dose of 2550 mg per day.

Regarding weekly titration for oral drug metering, the titration targets are fasting blood glucose (FBG) (3.9–5.6 mmol/L) and blood glucose at 2 h after each of the three meals (5.0–7.0 mmol/L). After meeting the above criteria, the participants will continue the medication for 3 months and then stop.

Routine diabetes health education will be provided to all participants during the treatment period. Routine diet control and appropriate exercises will be planned. Follow-up will be conducted monthly for the first 3 months after the end of treatment and every 3 months thereafter for 1 year (Table 1; Fig. 2). Participants with FBG > 7.0 mmol/L and postprandial blood glucose (PBG) > 10 mmol/L during the follow-up period are defined as having hyperglycemia recurrence, which will be treated according to the Chinese guidelines for the diagnosis and treatment of T2DM and is defined as not remitted.

**Table 1 Tab1:** Participant visit schedule

**Research Stage**	**Screening**	**Baseline**	**Intervention Period**				**Follow-up Period**		

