#### Safety outcomes

Participants will be followed up by telephone every month to inquire about their adverse reactions and events, and physical examinations, laboratory examinations as well as auxiliary detections will be conducted every three months. If there is a problem, take appropriate solutions and treatment measures, and record the situation in time.

Monitoring indexs: clinical symptoms; vital signs; electrocardiogram; blood and urine routine tests; liver and kidney functions; electrolyte levels; urinary albumin/creatinine ratio; myocardial enzyme profile; blood amylase level; thyroid function; eGFR; and blood/urine pregnancy test; and incidence of hypoglycemia, ketosis hypoglycemia and cardiovascular and cerebrovascular events.

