### Visits and measurements

#### Follow-up visit

At the beginning of treatment, participants will be required to visit the centre every week to report their blood glucose monitoring status, and receive adjustment of the dosage and frequency to achieve a fast and stable blood glucose standard. When the participant’s blood glucose level reaches the standard, the visit will be repeated every 2 ~ 4 weeks until the end of the treatment period. After drug withdrawal, participants will be followed up by telephone every month and return to the centre every 3 months until the end of follow-up.The specific follow-up items are shown in Table 1.

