### Sample size calculation

This is a controlled trial aims at exploring the remission effect of canagliflozin on T2DM. The experimental group is the canagliflozin group, and the control group is the metformin group. The main observation index is the remission rate. We referred to relevant studies and set the remission rate for metformin as 20.9%, similarly the estimated remission rate of canagliflozin was also 20.9%. For non-inferiority design, the cut-off value was 2%, α = 0.025, and power = 0.80. The sample size calculated by PASS 15 software was 73 cases in each group, and at least 92 participants should be enrolled in each group at baseline, for a total of 184 participants.

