### Data analysis

All statistical analyses will be performed by full-time statisticians using R Studio (Version 1.2.5001, R Studio Inc., Boston, MA, USA). The normality test will be used to determine whether the data are normally distributed. Continuous variables with a normal distribution will be reported as the mean ± SD, and ordinal and non-normally distributed variables will be reported as the median and interquartile range. Independent samples t-tests or Mann-Whitney U-tests will be used for comparisons, as appropriate. Categorical variables will be reported as counts and proportions, and the Pearson χ^2^ test or Fisher’s exact test will be used for comparisons, as appropriate.

The primary outcomes (remission rate 3 months after drug withdrawal and after 1 year of follow-up) will be compared between groups using Pearson’s χ^2^ test or Fisher’s exact test. Logistic regression will be used to adjust for potential confounders. Variables with P < 0.05 in the univariate comparisons, and known confounders that could impact the efficacy, will be included in the multivariable logistic regression models.

Subgroup analyses will be conducted of the primary outcomes stratified by age group (young, 18 ~ 35 years; middle-aged, 36 ~ 59 years; older, 60 ~ 65 years); duration of disease (<1 year, 1 ~ 2 years, 2 ~ 3 years); BMI (18.5 ~ 27.9 kg/m^2^, 28 ~ 40 kg/m^2^); and sex, using the same methods of analysis.

For the secondary outcomes, continuous data will be analyzed using the linear mixed effects model, which will use the random intercept model to explain the internal correlation of participants. Discontinuous data will be analyzed similar, but the generalized linear model appropriate to the distribution assumptions and link functions will be used. The analysis of all secondary outcome indicators also corrected for potential confounders (including variables with P < 0.05 in the univariate comparisons and known confounders that could have an impact on the efficacy). The safety indicators will be analyzed using the same methods used to analyze the main outcome indicators.

Missing values will be filled using multiple imputation methods, and sensitivity analyses will be performed.

Two-tailed P-values will be used, and P-values < 0.05 will be regarded as statistically significant. Point estimates will be reported with 95% confidence intervals.

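### All safety indicators are assigned the binary remission-rate methods, which fit events and abnormal-value counts but not repeated continuous laboratory values; the fallback is valid but uses neither baseline nor repeated visits

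*Protocol article*

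**What the plan says.** The Data analysis section gives one rule for safety: "The safety indicators will be analyzed using the same methods used to analyze the main outcome indicators". The Sample size calculation section identifies the main outcome: "The main observation index is the remission rate". Data analysis compares that rate between arms by Pearson's chi-square or Fisher's exact test, with logistic regression for adjustment. The adjustment set is variables with P < 0.05 in univariate comparisons plus known confounders of efficacy.

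Safety outcomes lists events (hypoglycemia, ketosis, cardiovascular and cerebrovascular events) together with laboratory measures, among them "liver and kidney functions; electrolyte levels; urinary albumin/creatinine ratio; myocardial enzyme profile; blood amylase level; thyroid function; eGFR". It gives no limits that would turn the laboratory values into abnormal/normal outcomes. On timing it says that "laboratory examinations as well as auxiliary detections will be conducted every three months".

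Two other rules in Data analysis bear on continuous data. The opening paragraph says, for continuous variables in general: "Independent samples t-tests or Mann-Whitney U-tests will be used for comparisons, as appropriate". A later paragraph gives continuous secondary outcomes a linear mixed model, "which will use the random intercept model to explain the internal correlation of participants".

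On drug exposure, Randomisation and interventions says: "After meeting the above criteria, the participants will continue the medication for 3 months and then stop". The Follow-up visit section adds: "After drug withdrawal, participants will be followed up by telephone every month and return to the centre every 3 months".

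**The concern.** The safety sentence is a stated choice of method, and it sends a list made up largely of continuous measurements to methods that need a categorical response. Read literally, it gives eGFR, liver and myocardial enzymes, electrolytes, albumin/creatinine ratio, amylase and thyroid function no analysis on their own scale.

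The general t-test/Mann-Whitney rule fills that hole. It does so with an unadjusted two-sample comparison that takes no covariate and does not link a participant's visits. In this trial the visits also differ in kind, because treatment stops by design and follow-up continues for a year. At stake are some precision in the laboratory comparisons and a stated plan for reporting on-treatment and post-withdrawal differences separately. The primary remission comparison and the comparison of safety events are not affected.

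**Working it through.** **1. Which methods the safety sentence points to.** Data analysis uses separate terms for primary and secondary outcomes, and the sentence immediately before the safety rule concerns the secondary ones. With the sample-size section naming the remission rate as the main index, the natural reading is chi-square or Fisher's exact test plus logistic regression. The mixed model is assigned to secondary outcomes only.

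**2. Method against type of measure.**

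| Safety measure | Assigned method (binary) | General rule (t-test/Mann-Whitney) | Mixed model (secondary outcomes only) |
|---|---|---|---|
| Hypoglycemia, ketosis, cardiovascular and cerebrovascular events | Fits | Not applicable | Not needed |
| Proportion with a laboratory value beyond a clinical limit | Fits, once limits are set | Not applicable | Not needed |
| Continuous laboratory values at repeated visits | Does not fit | Valid; no baseline, no link between visits | Fits, if baseline and arm-by-visit terms are added |

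Blood pressure and heart rate are listed among the secondary outcomes, so they already receive the mixed model and are outside this point.

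**3. Does either stated rule bring in the baseline value?** The two-sample tests cannot. Logistic regression could, but only if the baseline value passes P < 0.05 or is judged a known confounder, and that criterion is worded for efficacy. Neither rule prespecifies it.

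**4. Are baseline values available?** Largely yes. The exclusion criteria already require, at screening, eGFR, serum creatinine, alanine aminotransferase, bilirubin, creatine kinase and its isoenzyme, amylase and thyroid-stimulating hormone.

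**5. On-drug and off-drug visits.** Safety outcomes describes monthly telephone contact with examinations every three months. The Follow-up visit section gives that same pattern for the period after withdrawal, whereas treatment visits are weekly and then every 2 to 4 weeks. Many of the repeated laboratory values may therefore be off drug. The visit marks in Table 1 cannot be read reliably in the extracted text, so the number of on-treatment laboratory draws is not established here.

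**6. Size of the precision loss (illustrative).** The plan has no figure of its own to reproduce on this point. Inputs: 92 enrolled and 73 evaluable per arm (Sample size calculation). The baseline correlation ρ is an assumption, taken as 0.3, 0.5 and 0.7.

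- Unadjusted 95% half-width for an arm difference at one visit, in SD units: t × √(2/n).
  - n = 92: 1.973 × √(2/92) = 0.291
  - n = 73: 1.977 × √(2/73) = 0.327
- With the baseline value as covariate, multiply by √(1 − ρ²).

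| n per arm | Unadjusted | ρ = 0.3 | ρ = 0.5 | ρ = 0.7 |
|---|---|---|---|---|
| 92 | 0.291 | 0.278 | 0.252 | 0.208 |
| 73 | 0.327 | 0.312 | 0.283 | 0.234 |

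At ρ = 0.5, 92 × (1 − 0.25) = 69 participants per arm with baseline adjustment give the precision of 92 without it.

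**The case against.** The strongest reply is that Data analysis, read as a whole, already gives continuous variables a continuous test and categorical ones a categorical test, so the safety sentence is only a loose cross-reference. An unadjusted comparison of randomised arms is valid. Covariates and visit terms for safety laboratories are commonly left to an analysis plan. Comparing proportions with abnormal values is also ordinary safety reporting.

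Much of this stands. The fallback is valid, categorical summaries are legitimate and should stay, and missing model detail alone would not be a finding. What remains is that the protocol has fixed a family of methods for safety that does not fit most of its laboratory list. It has done so while holding a better-suited model a few lines above.

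Two stronger readings are tempting, and the documents support neither.

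- A reader might infer that a laboratory shift would be hidden, or that the values will be cut into categories with loss of power. The general rule lets them be summarised and compared as continuous data, and the article sets no cut-points.
- A reader might infer that on-drug differences will be diluted by pooling with off-drug values. Nothing in the plan averages across visits, and tests done visit by visit would keep the two periods apart. Pooling would arise more readily from the random-intercept model if it were used without arm-by-visit terms, which is why those terms belong in the fix.

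**Conclusion.** The point holds as a minor weakness. The method stated for safety fits events and abnormal/normal counts but not repeated continuous laboratory values. The general rule keeps the plan valid, so no result would be wrong; the cost is efficiency and clarity.

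At 92 per arm the half-width would fall from 0.29 SD to between 0.28 and 0.21 SD as the baseline correlation goes from 0.3 to 0.7, with 0.25 SD at 0.5. The documents do not give these correlations, and the calculation covers a single visit with equal variances and no missing values. The reading of the safety sentence as pointing to the binary methods rests on the sample-size section's use of the word main and on the contrast with secondary outcomes in Data analysis.

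**What to change.** Replace the safety sentence in Data analysis with wording along these lines:

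> Incidences of safety events, and proportions of participants with laboratory values beyond prespecified clinical limits, will be compared by chi-square or Fisher's exact test and logistic regression. Continuous safety laboratory values will be analysed with the random-intercept linear mixed model used for continuous secondary outcomes, with the baseline value as covariate and arm-by-visit terms. On-treatment and post-withdrawal differences between arms will be reported separately with 95% confidence intervals. Skewed values will be analysed on the log scale.

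Out-of-range proportions keep a formal comparison, since they are the clinically relevant summary and the binary methods suit them.

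The cost is a few sentences, using measurements already scheduled. The model is somewhat fuller than the one now stated for secondary outcomes, which names a random intercept and confounder adjustment but no baseline covariate or arm-by-visit terms. Clinical limits must also be listed. The downside is a few more safety estimates, to be read as estimates with intervals.

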#### Exit and withdrawal criteria

(1) Pregnant women or women planning for pregnancy.

(2) Intolerable adverse events.

(3) Worsening of blood glucose levels.

(4) Severe or repeated hypoglycemia.

(5) Pancreatitis.

(6) Participants who do not take medication nor accept testing as required.

(7) Participants who cannot complete the study as planned or have other factors that may affect the efficacy or safety evaluation.

(8) Participants who participate in other clinical trials during the trial.

(9) Participants who voluntarily withdraw from the study with informed consent.

(10) Participants who do not explicitly raise the request to withdraw from the test but no longer accept medication, testing, and follow-up.

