### Outcomes

#### Primary outcome

Remission rates.

This is the percentage of participants in each group who meet the remission criteria during follow-up: HbA1c < 6.5% maintained for > 3 months after the treatment discontinuation [27].

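### Participants who fail on glucose before planned drug discontinuation can be imputed as possible remitters, because the missing-data rule makes no exception by reason

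*Protocol article*

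**What the plan says.** Five sections of the protocol article bear on this.

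- **Exit and withdrawal criteria** lists "Worsening of blood glucose levels" among ten reasons for leaving, and also "Participants who do not take medication nor accept testing as required". It assigns no outcome to anyone who exits.
- **Randomisation and interventions** sets fasting and post-meal glucose targets for titration and continues: "After meeting the above criteria, the participants will continue the medication for 3 months and then stop". The article describes no other route to planned drug discontinuation.
- **The same section** handles recurrence. Participants with fasting glucose above 7.0 and postprandial glucose above 10 mmol/L "during the follow-up period are defined as having hyperglycemia recurrence", and this "is defined as not remitted".
- **Primary outcome** counts the share of each group whose participants satisfy the criterion in follow-up: "HbA1c < 6.5% maintained for > 3 months after the treatment discontinuation". Data analysis names the time points: "remission rate 3 months after drug withdrawal and after 1 year of follow-up".
- **Data analysis** gives the missing-data rule: "Missing values will be filled using multiple imputation methods, and sensitivity analyses will be performed".

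**The concern.** Exit for worsening glucose is informative about the primary outcome: such a participant is moving away from remission. Someone who leaves during titration or maintenance, or never meets the targets, has no HbA1c after planned drug discontinuation. If that HbA1c is treated as a missing value, the imputation draws at least partly on participants who did well enough to stay, and gives a glycaemic failure a non-zero probability of remission.

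Two things would follow. Each arm's remission rate would be too high. And if one drug loses more participants to poor control, imputation would hide part of that drug's disadvantage. In an open-label comparison of two different drugs, equal exit rates cannot be taken for granted.

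**Working it through.** **Step 1. Who has a defined outcome?**

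| Situation | Rule in the article | Outcome |
|---|---|---|
| Follow-up, both glucose thresholds exceeded | Recurrence rule | Not remitted; no imputation needed |
| Follow-up, one threshold exceeded, participant stays | HbA1c criterion, with three-monthly centre visits (Follow-up visit) | Decided by HbA1c |
| Follow-up, exit without both thresholds exceeded and before an HbA1c | None specific | Open: imputed, or not remitted |
| Exit for worsening glucose in titration or maintenance | None specific | Open |
| Targets never met, so drug never stopped as planned | None specific | Open |

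The last three rows are the gap. For them the imputation sentence points one way and a literal reading of Primary outcome points the other.

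**Step 2. Inputs from Sample size calculation.** Remission is 20.9% in both groups, with 73 per group raised to 92. The increase reproduces with a 20% loss: 73 / (1 − 0.20) = 91.25, rounded up to 92. That is 92 − 73 = 19 participants per arm. The 20% is implied, not stated. The article gives no number of exits for worsening glucose, so the counts below are assumptions, with 19 as the case where the whole implied loss is glycaemic.

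**Step 3. Overstatement in one arm.** Let w be the glycaemic exits, all truly not remitted, and q the imputed probability of remission.

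Overstatement = w × q / 92.

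With q = 20.9%:

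- w = 5: 5 × 0.209 = 1.0 false remitter; 1.045 / 92 = 1.1 points
- w = 10: 2.1 false remitters; 2.09 / 92 = 2.3 points
- w = 19: 4.0 false remitters; 3.971 / 92 = 4.3 points

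If those who stay remit at 20.9%, counting the exits as not remitted gives 0.209 × (92 − w) / 92 = 19.8%, 18.6% and 16.6%.

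Varying q from 10% to 30% widens the range to 0.5 points (5 × 0.10 / 92) up to 6.2 points (19 × 0.30 / 92).

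**Step 4. Unequal exits.** Take 5 exits in one arm and 15 in the other, with those who stay remitting at 20.9% in both.

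- Imputed at 20.9%: both arms show 20.9%, difference 0.
- Counted as not remitted: 0.209 × 87 / 92 = 19.8% and 0.209 × 77 / 92 = 17.5%, difference 2.3 points.

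For scale, the standard error of a difference at 92 per arm is √(2 × 0.209 × 0.791 / 92) = 6.0 points.

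**The case against.** The best defence is that nothing in the article says an exiting participant's outcome is set to missing. Primary outcome can be read as keeping everyone in the group denominator, so that a person who never meets the criterion is simply not remitted. Recurrence in follow-up is already classed that way, and the three-monthly visits mean that crossing one threshold does not by itself lose the HbA1c. The imputation model and the sensitivity analyses may properly sit in a fuller document. A model using the glucose values reported weekly in titration, and every 2 to 4 weeks afterwards, would give deteriorating participants a lower probability than 20.9%.

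Most of this stands, and it narrows the point to the three open rows above. It does not close them. The favourable reading of Primary outcome conflicts with an imputation rule that has no exceptions, and a better imputation model would still give known failures some chance of remission.

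A reader might go further and infer that the plan definitely imputes all withdrawn failures. The documents do not say so; that comes from combining the exit list with the imputation sentence. A reader might also take 0.209 / (1 − share exiting) as the imputed rate: 23.2%, 26.1% and 29.9% at 10%, 20% and 30% exits, hence spurious differences of 2.9 points (10% v 20%) and 6.6 points (10% v 30%), both above the 2% non-inferiority margin. The arithmetic is right, but these are complete-case rates. They assume that every exit is glycaemic and that imputation uses nothing but arm, and the exit shares are not in the documents. The ten exit reasons include pregnancy, adverse events and joining another trial, and non-adherence is not inherently driven by the outcome. The margin is also a weak yardstick: Data analysis specifies two-tailed tests and never applies it.

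**Conclusion.** The concern holds as a conflict between rules. For glycaemic failure before planned drug discontinuation, and for a smaller group who exit in follow-up, the article supports both imputation and non-remission. Followed as written, the imputation rule can turn some failures into remitters. If it does, the bias in each arm's rate is upward, and the comparison is biased when such exits differ by arm.

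The size is illustrative only. The 1.1 to 4.3 points rest on assumed counts of 5 to 19 exits and an imputed probability of 20.9%, and the top figure needs the whole implied 20% loss to be glycaemic. The hidden difference of 2.3 points for 5 v 15 exits is under half a standard error. It is a systematic error, though, and could be removed by wording.

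**What to change.** Reconcile Exit and withdrawal criteria, Randomisation and interventions, Primary outcome and Data analysis by stating that:

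1. the primary analysis includes all randomised participants in their assigned arm;
2. a participant who exits for worsening glucose, has recurrence, or never reaches drug discontinuation because the targets were not met counts as not remitted;
3. multiple imputation is kept for HbA1c missing for reasons unrelated to glycaemia, and the plan says on which side non-adherence falls;
4. scheduled HbA1c follow-up continues after exit from treatment where the participant agrees.

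This changes how outcomes are classified and collected, not how participants are treated. The cost is wording, follow-up visits for participants who exit treatment, and somewhat lower reported remission rates.

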### Study objectives

The primary objectives are to assess the effects of canagliflozin and metformin on diabetes remission and determine whether canagliflozin is superior to metformin. The secondary objective is to explore the possible underlying mechanisms by which the two medications elicit T2DM remission.

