#### Secondary outcomes

General physical characteristics, including weight, height, BMI, abdominal circumference, body composition, heart rate, and blood pressure.Blood glucose-related indexes: HbA1c, FBG, PBG, fasting insulin, fasting C-peptide, 2-h postprandial insulin, and 2-h postprandial c-peptide levels; homeostasis model assessment of insulin resistance; and homeostasis model assessment of β-cell function.Related indexes of lipid metabolism: plasma levels of triglycerides, total cholesterol, low-density lipoprotein cholesterol, and high-density lipoprotein cholesterol.Complications-related indicators: eye-ground photography, electromyography, and color doppler ultrasound of blood vessels in the neck and lower limbs.Visceral fat content: abdominal ultrasonography.Intestinal flora.Metabolomics.

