#### Biochemical measures

Participants will be required to fast at least 10 h before the study visit and return to the center between 6 and 10 am. They will be instructed to stop smoking and abstain from caffeine and alcohol 10 h before the study visit to ensure that all fasting blood samples are collected before taking medication in the morning. Biochemical tests, such as hematuria, will be completed at each center, and stool and blood samples of each participant will be collected and sent to professional institutions for the subsequent intestinal flora and metabolomics testing.

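### The single P < 0.05 rule also covers intestinal flora and metabolomics, which have no pre-specified features and no multiplicity control

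*Protocol article*

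**What the plan says.** The article's Study objectives section gives mechanism as the whole of the secondary objective: "The secondary objective is to explore the possible underlying mechanisms by which the two medications elicit T2DM remission". The Secondary outcomes list ends with two omics items, "Intestinal flora.Metabolomics", and names no feature for either. Under Biochemical measures, stool and blood samples are "sent to professional institutions for the subsequent intestinal flora and metabolomics testing"; no assay, panel or number of features is described.

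The Data analysis section gives these outcomes no method of their own. It says: "For the secondary outcomes, continuous data will be analyzed using the linear mixed effects model", with a generalized linear model for data that are not continuous. The only correction it mentions is for covariates: "The analysis of all secondary outcome indicators also corrected for potential confounders". It then sets one decision rule for everything: "Two-tailed P-values will be used", and "P-values < 0.05 will be regarded as statistically significant". Neither a multiplicity adjustment nor an exception for the omics outcomes is stated.

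**The concern.** Weight or HbA1c is one variable, so a 0.05 criterion has its usual meaning there. Whether a handful of such clinical secondary outcomes should be adjusted is a matter on which statisticians differ. Flora and metabolomics results usually come as sets of taxa and metabolites, each of which can be tested. With the feature list open and a per-test threshold of 0.05, the number of features called significant grows with the size of the panel even when the drugs do not differ on any of them.

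At stake is the omics part of the mechanism objective. The Abstract's Discussion paragraph expects the trial to yield strong evidence on mechanism as well as efficacy. A list of taxa or metabolites selected by this rule could not carry that weight, because the reader would have no means of telling real differences from chance ones.

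**Working it through.** The article gives no number of features and no expected number of false findings, so there is no figure of its own to reproduce on this point.

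**Inputs**
- Per-test significance level: 0.05, two-sided (Data analysis).
- Number of tested features, M: not stated. Assumed here to range from 20 to 500, with one between-group test per feature.
- Truth: no feature differs between the arms (all null hypotheses true).

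**Expected number of false positives** = 0.05 × M. This needs no independence assumption.
- M = 20: 0.05 × 20 = 1
- M = 50: 0.05 × 50 = 2.5
- M = 100: 0.05 × 100 = 5
- M = 200: 0.05 × 200 = 10
- M = 500: 0.05 × 500 = 25

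**Chance of at least one false positive** = 1 − 0.95^M. This does assume independent tests; correlation between features changes it.
- M = 20: 1 − 0.95^20 = 0.642, or 64%
- M = 50: 1 − 0.95^50 = 0.923, or 92%
- M = 100: 1 − 0.95^100 = 0.994, or 99.4%

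**Under the proposed rule.** Benjamini-Hochberg at 5% orders the M P-values within a panel, finds the largest rank k whose P-value is at most 0.05 × k/M, and declares the features at ranks 1 to k significant. If all nulls are true and the tests are independent, the chance of any discovery in that panel is at most 5%, against 99.4% at M = 100 under the present rule.

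**Repeated visits.** The planned mixed model with a random intercept can use all visits of a feature in one model. The number of tests therefore need not be multiplied by the number of visits, and M above is not inflated in that way.

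**The case against.** The best defence is that the closing sentence is generic. It does not say that the P-values are raw, does not mention omics, and could be read as applying 0.05 to adjusted values. A journal article is condensed, and feature filtering and false-discovery control are often left to a statistical analysis plan or laboratory plan, which is not shown here. The objective is also worded as exploratory.

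Part of this stands. The article never uses the word unadjusted; that is the plain reading of a single threshold with no multiplicity method, not a statement in the text. But the point does not rest on a missing detail alone. The section fixes a threshold and routes every secondary outcome to it. It is also not a bare outline, since it gives subgroup cut-points, the covariate-selection rule, the random-effects structure and the handling of missing data. Nor does exploratory wording in the objectives help while Data analysis attaches the label of statistical significance without qualification.

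A reader might infer more than the article supports:
- **Dozens of false signals should be expected.** A count of 24 needs 24 / 0.05 = 480 tested features. No count is given, and panels of 20 to 200 features give 1 to 10.
- **The mechanism objective rests mainly on these panels.** The Background builds the mechanism on weight loss, fat deposition, insulin resistance and β-cell function. The Secondary outcomes list includes body composition, HOMA indices, insulin, C-peptide and visceral fat. Flora and metabolomics are the last two of seven items.
- **Visits and covariate-adjusted models multiply the error.** One mixed model per feature need not do so, and adjusted and unadjusted tests of the same feature are correlated.

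**Conclusion.** The concern holds in a limited form. The stated 0.05 rule, with no multiplicity control, suits the flora and metabolomics outcomes badly, because no feature is pre-specified for either. Under the global null it would give about 1 false signal at 20 features, 5 at 100 and 25 at 500. With independent tests, at least one false signal is more likely than not at 20 features and close to certain at 100. These sizes rest on assumed feature counts and on features being tested one by one, neither of which the article states. If flora were summarised by a few indices, that panel's problem would be small.

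The consequence is confined to omics-based mechanism claims. The primary remission comparison is not affected, and the article gives no reason to demand that significance statements be withdrawn from the other secondary outcomes.

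**What to change.** Add to the Data analysis section, directly after the 0.05 criterion, a sentence to this effect: for intestinal flora and for metabolomics, a feature will be declared significant only after Benjamini-Hochberg false-discovery-rate control at 5%, applied separately within each panel, and these results will be reported as hypothesis-generating. If a statistical analysis plan already contains such a rule, the sentence only needs to point to it.

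The cost is one sentence and a one-line adjustment in R. The sample size, data collection and the handling of the other secondary outcomes do not change. The downside is that fewer features will be flagged, and some real but modest differences may be missed. The change should be recorded before the omics results are analysed.
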